| Blood Sampling Schedule        | Safety blood tests (FBC, coagulation screen and clinical chemistry) as per schedule (table 1)
HIV, hepatitis B & hepatitis C antibody blood tests at screening
Exploratory immunology tests at screening, as per schedule (table 1)
HLA testing at day 0                                                                                                                                                     |
| Primary Evaluation Criteria    | Actively and passively collected data on adverse events                                                                                                                                                                                                                                                                                                                                                               |
| Secondary Evaluation Criteria  | Laboratory markers of cell mediated immunity in blood and bronchoalveolar lavage samples                                                                                                                                                                                                                                                                                                                              |

| Attendance number                               | 1  | 2   | 3   | 4    | 5   | 6   | 7   | 8    | 9   | 10  | 11  |
|-------------------------------------------------|----|-----|-----|------|-----|-----|-----|------|-----|-----|-----|
| Timeline (days)*                                | S  | 0   | 2   | 7    | 14  | 28  | 30  | 35   | 42  | 84  | 168 |
| Timeline (weeks)*                               | S  | 0   |     | 1    | 2   | 4   |     | 5    | 6   | 12  | 24  |
| Time windows (days)                             |    |     | ±1  | -2+3 | ±4  | ±5  | ±1  | -2+3 | ±4  | ±14 | ±21 |
| Inclusion/exclusion criteria                    | X  |     |     |      |     |     |     |      |     |     |     |
| Review contra-indications                       | X  | X   |     | X    |     | X   |     | X    |     |     |     |
| Informed consent                                | X  |     |     |      |     |     |     |      |     |     |     |
| Medical history                                 | X  | (X) | (X) | (X)  | (X) | (X) | (X) | (X)  | (X) | (X) | (X) |

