## Bronchoscopy and bronchoalveolar sampling

Protection from TB induced by intra-pulmonary vaccination correlates with cellular immune responses detected in the bronchoalveolar lavage (BAL) samples of immunised mice (57). In macaques receiving aerosolised MVA85A we detected significant levels of antigen-specific cellular immune responses in bronchoalveolar lavage samples (35). These pre-clinical findings provide the rationale for wishing to obtain BAL samples from our clinical trial subjects.

BAL samples are obtained by performing a bronchoscopy, which is a widely and safely used procedure in clinical research studies involving both healthy subjects and subjects with respiratory diseases such as asthma (58, 59). Clinical guidelines for performing investigative bronchoscopy in research studies are well established (60). The short procedure involves the insertion of a narrow flexible fibre-optic tube into the airway under light intravenous sedation. Under direct vision saline is delivered to a section of lung mucosa and then recollected by suction. In clinical trial TB026 bronchoscopies were well tolerated by volunteers.

Bronchoscopy is an essential component of this clinical trial because BAL samples are the ideal method to analyse the lung mucosal cellular immune responses which we intend to induce by vaccination (61). Clinical trials of intranasal vaccine candidates for other infectious diseases have analysed humoral immunity within nasal lavage, but a cellular immune response is essential for protective immunity against *M. tb* (62). It is unlikely that administering a vaccine intranasally in humans would result in the induction of a significant cell mediated immune response in the lower airways. Nasal mucosal samples are unlikely to provide adequate cellular samples as nasal lavage generally yields insufficient and variable numbers of cells (63). Furthermore as the vaccine is nebulised and inhaled orally we do not expect it to reach the nasal mucosa.

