| Secondary Objectives
To characterise mucosal and systemic immunogenicity of viral vector (MVA) and insert (Ag85A) by comprehensive characterisation of humoral and cellular immune responses

Evaluate functional relevance of anti-vector immunity induced by aerosol and systemic immunisation in MVA85A-prime followed by homologous MVA85A-boost administered 4 weeks after the MVA85A-prime | 

1. Induction of humoral and cell-mediated immunity to MVA by aerosol and systemic immunisation

2. Induction of cell-mediated and humoral immunity to Ag85A by aerosol and systemic immunisation

3. Effect of a boosting immunisation one month after prime on humoral and cell-mediated immunity to insert (Ag85A) and vector (MVA)

 |

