#### ***Trial groups***

This will be a Phase I clinical trial with a standard dose of MVA85A (pfu) in 3 groups of 12 volunteers with 3 different route permutations for boosting (see Table 3).

The overall investigational approach with our MVA85A trials is to develop an effective prime-boost vaccination strategy to prevent TB infection, with BCG as the priming vaccine.

This Phase I trial will have 3 treatment arms (homologous):

| Group | Route of priming MVA85A | Bronchoscopy 1 week later | Route of boosting MVA85A | Bronchoscopy 1 week later |
|-------|-------------------------|---------------------------|--------------------------|---------------------------|
| 1     | Aerosol                 | Yes                       | Systemic                 | Yes                       |
| 2     | Systemic                | Yes                       | Aerosol*                 | Yes                       |
| 3     | Systemic                | Yes                       | Systemic                 | Yes                       |

Table 3: Route of immunisations and timing of bronchoscopy

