#### **\* Change to Group 2 vaccinations**

A change has been made for group 2 volunteers due to receive their day 28 boost vaccination on or after 2 September 2015, due to a higher frequency of mild respiratory adverse events in this group. Local (skin) and systemic symptoms were as expected and consistent with data from previous studies. These volunteers will not receive the day 28 boost vaccination, but instead will receive a placebo by both intradermal and aerosol inhaled routes to maintain blinding. Additional safety and immunological information will be gained by continuing with day 35 bronchoscopy in these volunteers. Any volunteer not wishing to proceed in this manner will remain in follow up with no vaccination or bronchoscopy.

As BCG is protective in childhood, it is routinely given at birth in TB endemic countries but is also in widespread use in children and adolescents in much of the rest of the world. Therefore, as in previous trials of intradermal MVA85A, we propose to vaccinate BCG-primed subjects. These will be healthy men and women aged 18-55 years who have been previously vaccinated with BCG.

All subjects will have received BCG vaccination at least six months prior to enrolment. MVA85A ( $5 \times 10^7$  pfu) or saline placebo will be administered by systemic (intradermal) or aerosol (Omron jet nebuliser) route (paired placebo design). The interval between the two vaccinations is one month.

In order to minimise the risk from bronchoscopy, subjects with a history or evidence of lung disease will be excluded. This will be determined by our standard screening procedures (history, examination, urine analysis, and blood tests), and, in addition, a chest x ray and pulmonary function testing.

The peak effector T-cell response in blood is ~7 days post-vaccination with MVA85A. Pulmonary mucosal responses are expected to follow a similar time course and a preclinical study has demonstrated this in non-human primates (35). Thus bronchoscopy and bronchialveolar lavage will be performed seven days after each vaccination.

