## 4.2 Randomisation

In order to reduce bias and the influence of any difference in the baseline characteristics between the three groups, we have chosen to randomise the allocation of subjects. This aims to achieve a balance between the three groups in any important confounding factors such as levels of pre-existing antimycobacterial immunity (influenced by, for example, country of origin and length of time elapsed since prior BCG vaccination). This will be performed by variable block randomisation using sequentially numbered sealed envelopes, prepared by an independent colleague at the Centre for Statistics in Medicine, to ensure allocation concealment. Volunteers are blinded as they will receive a paired placebo at the same time of vaccination. The bronchoscopist will be blinded to the route of vaccine administration. This is intended to eliminate any bias in the reporting of the appearance of the lung mucosa and extent of airway inflammation. In addition, the postdoctoral researcher in the laboratory overseeing the immunological analyses will also be blinded to reduce any bias that could be introduced at the sample processing stage. All samples will be anonymised.

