# **9. STATISTICS**

## **9.1 Statistics**

This is primarily a trial with descriptive endpoints. Twelve subjects will be recruited into each arm of the trial (i.e. 36 in total). Our previous experience with clinical trials using MVA85A over the last 10 years suggests that this sample size is a feasible number to recruit, screen, enroll, and follow up in practical terms, whilst also allowing the determination of any substantial and clinically significant differences in safety and cell-mediated immunity between the three groups. A twofold increase in the magnitude of the cellular immune response (as measured by Elispot response to 85A peptide stimulation) is considered immunologically meaningful. Extrapolating effect size and variability from the completed initial aerosol vaccine safety study (TB026), twelve volunteers are needed to have 80% power to detect an immunologically meaningful difference in the summed peptide pools and 8

volunteers to achieve the same for single peptide pool of 85A. This sample size is appropriate for a proof-of-concept Phase I safety study.

It is anticipated that the immunological endpoints will not follow a normal distribution. A log transformation will be applied and if the resulting data are normally distributed they will be summarised by group using means and standard deviations. The one-week and six-month responses will be compared between the three groups using a t-test. If the resulting data are not normally distributed then medians and interquartile ranges will be used to summarise the data and the Mann Whitney U test will be used for statistical comparisons. An area-under-curve analysis will be used to compare the overall responses over time between the three groups. This analysis will make use of data collected at all time points.

Differences between means or medians between the three groups will be presented along with their 95% confidence intervals. Within each group, paired data will be analysed using either a paired t-test or the Wilcoxon matched pairs test depending on the normality of the data.

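### Lavage is taken only after vaccination, so in the lung the trial can estimate a level and a between-route difference, but not induction from baseline

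*Protocol*

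**What the plan says.** - **Objective and endpoints (section 3).** The first secondary objective covers the mucosal and systemic response to both vector and insert. The endpoints beside it are worded as induction by each route; the one for the insert is "Induction of cell-mediated and humoral immunity to Ag85A by aerosol and systemic immunisation".
- **Compartments (section 1).** The secondary evaluation criteria are "Laboratory markers of cell mediated immunity in blood and bronchoalveolar lavage samples".
- **Role of lavage (section 2.1).** The protocol states that "BAL samples are the ideal method to analyse the lung mucosal cellular immune responses which we intend to induce by vaccination".
- **Timing (section 4.1, Tables 1 and 3).** "Thus bronchoscopy and bronchialveolar lavage will be performed seven days after each vaccination". Table 3 gives every group two procedures, each headed "Bronchoscopy 1 week later". Table 1 marks bronchoscopy at days 7 and 35 only. It schedules blood for exploratory immunology at screening, at day 0 and at every later visit.
- **Population (sections 2.1, 4.1, 4.2).** All volunteers have had BCG, and section 2.1 says that BCG expresses antigen 85A. Section 4.2 randomises to balance "any important confounding factors such as levels of pre-existing antimycobacterial immunity".
- **Analysis (section 9.1).** One-week and six-month responses are compared between the three groups, with 95% confidence intervals for the differences. "Within each group, paired data will be analysed using either a paired t-test or the Wilcoxon matched pairs test", with neither compartment nor time points named.
- **Group 2 amendment (sections 4.1 and 6.1).** Group 2 volunteers whose boost fell due on or after 2 September 2015 receive saline by both routes on day 28 and, unless they decline, still have the day 35 bronchoscopy.

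**The concern.** Induction means a rise caused by the vaccine. Showing one needs either a value from before vaccination or a concurrent unvaccinated group. Lavage has neither, in people whose earlier BCG could already have left an 85A response.

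Two conclusions are at stake. A day 7 lavage response in the intradermal arms could be put down to the vaccine when some or all of it was there before. And if the section 9.1 paired test is run on lavage, it compares two samples that both follow the prime. A strong prime response that had faded by day 35 could even appear as a fall.

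The concern is limited to lavage. The same endpoint wording also covers blood, where induction can be estimated.

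**Working it through.** **1. What each compartment offers (Table 1)**

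| | Before vaccination | After prime | After day 28 |
|---|---|---|---|
| Blood | screening, day 0 | days 2, 7, 14, 28 (day of boost) | days 30, 35, 42, 84, 168 |
| Lavage | none | day 7 | day 35 |

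Volunteers with a pre-vaccination lavage: 0 of 36. Arms unvaccinated at day 7: 0 of 3.

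**2. What a day 7 lavage value identifies**

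Write the day 7 level as b + d, with b the response before vaccination and d the induction by the prime. Only the sum is observed. A level of 100 (arbitrary units) fits each of these equally well:

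| b | d | Fold rise, 100/b |
|---|---|---|
| 25 | 75 | 4.0 |
| 50 | 50 | 2.0 |
| 75 | 25 | 1.33 |
| 100 | 0 | 1.0 (none) |

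These baselines are assumptions; the protocol gives no figure for lung. In blood, day 7 minus day 0 gives d directly.

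**3. What the lavage pair identifies**

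Let w be the share of the prime response still present at day 35 and e the effect of the boost.

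- Day 35 minus day 7 = (b + w·d + e) − (b + d) = e − (1 − w)·d.
- b cancels, so the change is the same for every row of the table in step 2 that shares the same day 35 level. The pair cannot show whether the prime induced anything.
- It mixes the boost effect with waning since the prime.
- With saline by both routes on day 28, e = 0 and only waning remains.

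**4. What randomisation does identify**

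Up to day 28, Groups 2 and 3 receive identical dosing: intradermal MVA85A with inhaled saline. Day 7 is therefore a two-way comparison by prime route, Group 1 (12) against Groups 2 and 3 (12 + 12 = 24). Of the three pairwise comparisons, 1 v 2 and 1 v 3 estimate the same quantity, and 2 v 3 has an expected difference of zero.

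Because b is balanced in expectation, the absolute difference equals the difference in induction. The ratio does not. With assumed inductions of 200 (aerosol) and 50 (intradermal), the observed ratio (b + 200)/(b + 50) is 4.0, 3.0, 2.5, 2.0 and 1.6 for b = 0, 25, 50, 100 and 200.

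**5. Power of the day 7 contrast**

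The protocol's figure is 12 volunteers for 80% power to detect a twofold difference in summed 85A ELISPOT. It states no SD, alpha or sidedness, so the figure can only be solved backwards. Taking ln 2 = 0.693, alpha 0.05 two-sided and 12 per group, the implied SD(ln) is 0.579 (noncentral t) or 0.606 (normal formula).

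I carry SD(ln) = 0.578 over to lavage as an assumption:

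- 12 v 12: standard error 0.578·√(1/12 + 1/12) = 0.236; noncentrality 0.693/0.236 = 2.94 on 22 df; power 80%.
- 12 v 24: standard error 0.578·√(1/12 + 1/24) = 0.204; noncentrality 0.693/0.204 = 3.39 on 34 df; power 91%.

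The same formula over a range of SDs:

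| SD(ln) | 12 v 12 | 12 v 24 |
|---|---|---|
| 0.5 | 90% | 97% |
| 0.578 | 80% | 91% |
| 0.7 | 64% | 78% |
| 0.8 | 53% | 66% |
| 1.0 | 37% | 48% |

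**The case against.** - **The endpoint does not say mucosal.** True. It covers blood as well, where induction is estimable, so the sentence is not wrong as a whole. But the objective beside it is partly mucosal, the criteria name lavage, and section 2.1 gives lavage as the method for lung responses that vaccination is meant to induce. The gap in the lung stands.
- **Nothing says that the results will be misread.** Also true. A reader might infer that the protocol plans to report day 7 lavage in the intradermal arms as mucosal induction, or to treat day 35 against day 7 as response against baseline. The text supports neither: section 9.1 names no compartment or time points for the pairs, and it calls the trial primarily descriptive. The choice of pairs can be left to a statistical analysis plan. No such plan can supply a baseline that was never sampled.
- **Much of the remedy is already there.** Section 9.1 already compares one-week responses between groups with confidence intervals, and the third secondary endpoint already concerns the boost. That stands. What is missing is the grouping by prime route and the limit on what lavage can show.
- **Randomisation handles prior immunity.** It does for the difference between routes. It cannot show that either route raised the response.
- **The lung background may be small.** It may be. The protocol does not locate pre-existing immunity in the lung, it suggests that systemic BCG may serve the lung poorly, and it excludes ELISPOT-positive latent infection. A reader might infer that a material BCG response in lavage is established; it is not. Nor is its absence.

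**Conclusion.** The point holds for lavage only. No volunteer and no arm provides an estimate of induction from baseline in the lung, and the lavage pair carries no information on induction by the prime. This follows from the sampling schedule and needs no numerical assumption.

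How much it matters in practice cannot be sized, because the protocol gives no figure for 85A response in the lung before vaccination. The randomised day 7 difference between routes remains valid. The power figures rest on an SD solved backwards from the sample size statement, a two-sided 5% test, and lavage being as variable as the ELISPOT response behind that statement; 91% falls to 66% if the SD is 0.8.

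It affects one compartment of a secondary objective, not the primary safety objective. It is still worth correcting, because local immune responses are central to the trial's rationale.

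**What to change.** No extra bronchoscopy is needed.

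1. **Day 7 lavage.** Replace the separate three-group comparisons with one randomised contrast by prime route, Group 1 against Groups 2 and 3 combined, with its 95% confidence interval. Section 4.3 describes a staged restart of Group 2 enrolment, so some of Group 2 may not be concurrent with the other arms. Repeat the contrast against Group 3 alone (12 v 12) as a sensitivity analysis.
2. **Day 35 against day 7 in lavage.** Describe it as post-boost against post-prime, confounded with time since the prime, and only in volunteers who received an active day 28 boost. Analyse Group 2 volunteers given saline by both routes on day 28 separately, as a second post-prime sample.
3. **Wording.** Confine induction from baseline to blood. Report within-arm lavage results as post-vaccination levels.

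The cost is a change to endpoint and analysis text. The downside is that the trial cannot claim, from lavage alone, that a single route, in particular the intradermal one, induced lung responses.

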## 4. TRIAL DESIGN

### 4.1 Trial Overview

This is a Phase I clinical trial where subjects are randomised to 3 different groups of homologous MVA85A boosts by either intradermal or aerosol route of vaccination to evaluate safety and immunogenicity of homologous boosting by heterologous routes of immunisation.

#### ***Trial groups***

This will be a Phase I clinical trial with a standard dose of MVA85A (pfu) in 3 groups of 12 volunteers with 3 different route permutations for boosting (see Table 3).

The overall investigational approach with our MVA85A trials is to develop an effective prime-boost vaccination strategy to prevent TB infection, with BCG as the priming vaccine.

This Phase I trial will have 3 treatment arms (homologous):

| Group | Route of priming MVA85A | Bronchoscopy 1 week later | Route of boosting MVA85A | Bronchoscopy 1 week later |
|-------|-------------------------|---------------------------|--------------------------|---------------------------|
| 1     | Aerosol                 | Yes                       | Systemic                 | Yes                       |
| 2     | Systemic                | Yes                       | Aerosol*                 | Yes                       |
| 3     | Systemic                | Yes                       | Systemic                 | Yes                       |

Table 3: Route of immunisations and timing of bronchoscopy

#### **\* Change to Group 2 vaccinations**

A change has been made for group 2 volunteers due to receive their day 28 boost vaccination on or after 2 September 2015, due to a higher frequency of mild respiratory adverse events in this group. Local (skin) and systemic symptoms were as expected and consistent with data from previous studies. These volunteers will not receive the day 28 boost vaccination, but instead will receive a placebo by both intradermal and aerosol inhaled routes to maintain blinding. Additional safety and immunological information will be gained by continuing with day 35 bronchoscopy in these volunteers. Any volunteer not wishing to proceed in this manner will remain in follow up with no vaccination or bronchoscopy.

As BCG is protective in childhood, it is routinely given at birth in TB endemic countries but is also in widespread use in children and adolescents in much of the rest of the world. Therefore, as in previous trials of intradermal MVA85A, we propose to vaccinate BCG-primed subjects. These will be healthy men and women aged 18-55 years who have been previously vaccinated with BCG.

All subjects will have received BCG vaccination at least six months prior to enrolment. MVA85A ( $5 \times 10^7$  pfu) or saline placebo will be administered by systemic (intradermal) or aerosol (Omron jet nebuliser) route (paired placebo design). The interval between the two vaccinations is one month.

In order to minimise the risk from bronchoscopy, subjects with a history or evidence of lung disease will be excluded. This will be determined by our standard screening procedures (history, examination, urine analysis, and blood tests), and, in addition, a chest x ray and pulmonary function testing.

The peak effector T-cell response in blood is ~7 days post-vaccination with MVA85A. Pulmonary mucosal responses are expected to follow a similar time course and a preclinical study has demonstrated this in non-human primates (35). Thus bronchoscopy and bronchialveolar lavage will be performed seven days after each vaccination.

